### Statistical Analysis

The primary analysis involves comparing the change in VAS from baseline to 48 weeks between the dienogest 1 mg/day group and 2 mg/day group using the mean difference and its 95% CI. When the lower limit of confidence exceeds –15 (noninferiority margin), the noninferiority of the effect of the 1-mg group to the 2-mg group will be recognized.

For the secondary efficacy endpoint, each of the dienogest 1 mg/day group and the 2 mg/day group will be compared to estimate the difference and its 95% CI for the mean value of dysmenorrhea score and change in endometriotic cyst size from baseline to 48 weeks.

In the safety evaluation, the frequency of low estrogen symptoms during the study treatment period is aggregated, and a 95% CI is calculated that is based on a normal approximation of the binomial distribution. In addition, a chi-square test will be used to compare groups. The 2-sided significance level is 5%.

The frequencies of the occurrence of adverse events and side effects are calculated for the safety analysis target population. As a secondary safety analysis, each of the dienogest 1 mg/day group and 2 mg/day group will be compared to estimate the difference and its 95% CI for the mean value of bone density, Kupperman score, and estrogen concentration. Statistical analyses are performed by R (version 4.1.0; R Foundation for Statistical Computing).

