### Data Collection and Study Procedures

The study data will be collected through a combination of patient questionnaires (Multimedia Appendices 2 and 3), laboratory tests, bone density measurements, and imaging studies, including preregistration magnetic resonance imaging scans and ultrasound examinations.

Once eligibility is confirmed, study personnel will input patient information into the electronic data capture system to facilitate enrollment and randomization. Randomization using the permuted block method with a block size of 2 or 4 will be stratified based on allocation factors, such as patient age and the presence or absence of uterine adenomyosis.

Treatment will commence on the second to fifth day of the first menstrual cycle following enrollment. Patients will be randomly assigned to receive either dienogest 0.5 mg (1 mg/day group) or dienogest 1 mg (2 mg/day group), administered orally twice daily for up to 48 weeks. Follow-up visits will be scheduled at 4 weeks post enrollment and every 12 weeks thereafter.

At each follow-up visit, comprehensive assessments will be conducted, including patient questionnaires, vital sign measurements, blood tests, and ultrasound examinations to evaluate the size of ovarian endometriotic cysts. A magnetic resonance imaging scan will be performed before study enrollment to establish baseline imaging data. Pain symptoms and estrogen-deficiency symptoms will be assessed through standardized questionnaires. Dysmenorrhea-related pain will be evaluated using the visual analog scale (VAS) and a modified dysmenorrhea score based on Harada et al [20] (Table 1).

The dysmenorrhea score (total score: 0 to 6) is the sum of the subscores on the severity of pain and the use of analgesics.

Estrogen-deficiency symptoms will be assessed using the Kupperman score (Table 2).

**Table 1 table1:** Dysmenorrhea score.

Degree		Definition	Score	

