### Study Endpoints

The primary efficacy endpoint is the change in VAS from baseline to 48 weeks after administration. The secondary endpoint of effectiveness evaluation is the amount of change in the dysmenorrhea score from baseline to 48 weeks after administration. Another secondary endpoint is the rate of reduction in the size of ovarian endometriotic cysts from the baseline to 48 weeks after administration.

For safety evaluation, an important safety endpoint is the incidence of symptoms related to low estrogen (symptoms other than those listed in the Kupperman score) during the study treatment phase. Symptoms are listed in question number 5 of the questionnaire (Multimedia Appendix 3).

Other safety endpoints include the amount of change in the Kupperman score, the rate of change in bone density, and the amount of change in blood estradiol concentration from baseline to 48 weeks after administration.

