### Sample Size

Based on a Japanese study [21], the mean change in VAS after 52 weeks with 1 mg dienogest was –52.1 (SD 24.13) for secondary dysmenorrhea. In the Japanese phase II dose-finding study, [19] the average change in VAS was –35.74 at 0.25 mg×2, –44.31 at 0.5 mg×2, and –50.78 at 1 mg×2 at 12 weeks. Therefore, it is assumed that at least an effect of 0.25 mg×2 or more can be expected by this test administration, and the noninferiority margin is set to 15. It is assumed that the effects of the 1 mg group and the 2 mg group are similar, and SD is assumed to be 24.13 with reference to the Japanese phase III study. [22] In the above setting, 41 cases in each group (82 cases in total) are required to achieve a power of 80% at a one-sided significance level of 2.5%. When 5% of dropout cases are added to each group, the required sample size becomes 44 cases in each group (88 cases in total).

We evaluated the incidence of low estrogen symptoms during the study treatment period as an important secondary endpoint. On the basis of the long-term use of dienogest [23], we assumed the incidence proportion for dienogest 1 mg/day and 2 mg/day to be 20% and 50%, respectively, with the chi-squared test providing more than 80% power at a 2-sided significance level of 5%. Therefore, the sample size in this study (88 cases in total) is also sufficient to assess the incidence of low estrogen symptoms.

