### Limitations

This study has several limitations. First, only patients with ovarian endometriotic cysts were included, excluding cases of endometriosis without ovarian involvement. This selection criterion was implemented to ensure diagnostic accuracy and maintain a homogeneous study population. However, future studies may be needed to evaluate the effects of long-term dienogest therapy in patients with other forms of endometriosis.

Second, as it was not conducted as a double-blind trial, there is a potential risk of bias in VAS and dysmenorrhea score evaluations.

This study was conducted within the framework of Japan’s health insurance system, which required specifying the prescribed drug formulation (0.5-mg or 1-mg tablet). Consequently, blinding was not feasible, and an open-label design was adopted. To minimize bias, we implemented 3 key measures. First, objective assessments, including ultrasound imaging, hormone levels, and bone density, were incorporated as primary endpoints to reduce reliance on subjective pain evaluations. Second, centralized randomization via an electronic data capture system was used to eliminate selection bias. Third, covariate adjustment for age and adenomyosis presence ensured balanced group allocation. These strategies enhance the study’s validity and reliability.

Given that endometriosis often requires long-term treatment until menopause, evaluating the efficacy and safety of extended dienogest administration is crucial. Although the observation period of this study is limited to 48 weeks, it provides valuable data, as no previous study has examined the effects of 1 mg/day beyond 12 weeks. Further research with extended observation periods is necessary to assess long-term efficacy and safety.

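### The primary analysis is stated as a simple difference in mean VAS change; adjusting for baseline VAS, age and adenomyosis would add precision at no cost in patients, and the Limitations wording on covariate adjustment needs reconciling

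*Protocol article*

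**What the plan says.** All references are to the protocol article.

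- **Study Endpoints:** "The primary efficacy endpoint is the change in VAS from baseline to 48 weeks after administration". A baseline VAS is therefore needed for every patient who contributes to the endpoint.
- **Statistical Analysis:** the primary comparison is made "between the dienogest 1 mg/day group and 2 mg/day group using the mean difference and its 95% CI". Noninferiority is declared if the lower limit lies above –15. Neither this analysis nor any other in the section mentions a covariate, a stratified method or a model.
- **Data Collection and Study Procedures:** randomisation uses permuted blocks and "will be stratified based on allocation factors, such as patient age and the presence or absence of uterine adenomyosis".
- **Sample Size:** the margin is 15, the SD of change is taken as 24.13 from an earlier Japanese trial, and the two doses are taken to have equal effects. This leads to 41 per group for 80% power at one-sided 2.5%, and to 44 per group after 5% dropout.
- **Limitations:** among the measures against bias in an open-label trial, "Third, covariate adjustment for age and adenomyosis presence ensured balanced group allocation".
- **Results:** 88 patients are enrolled, data collection is complete and the data are being prepared for analysis.

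**The concern.** There are two linked issues.

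**Precision.** Change from baseline is usually correlated with the baseline itself, and here entry requires dysmenorrhea but no minimum VAS, so baseline may vary widely. A plain difference in mean change leaves that variation in the error term. It also leaves any chance difference between the arms in baseline VAS in the estimate. In a noninferiority test the width of the interval decides the result directly, so avoidable width is lost power. The two stratification factors are also known for every patient, and leaving them out of the analysis generally makes the interval somewhat too wide.

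**Consistency.** The Limitations section presents covariate adjustment as a safeguard, but no analysis in the Statistical Analysis section includes it. It also credits adjustment with balancing the allocation, which is something stratified randomisation does and an analysis model cannot do. A reader cannot tell whether an adjusted analysis is intended.

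**Working it through.** **Inputs from the article:** margin 15, SD of change 24.13, true difference 0, one-sided alpha 2.5%, power 80%, 41 evaluable per group, 5% dropout. **Input not in the article:** r, the correlation of baseline VAS with change, taken over 0 to 0.6 in absolute value. The margin and the SD are taken to be on the same scale.

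**Step 1. Reproduce the stated sample size with an unadjusted formula.**
n per group = 2 × (1.960 + 0.842)² × 24.13² / 15² = 40.6, rounded up to 41.
Dropout: 41 / 0.95 = 43.2, rounded up to 44 per group, 88 in total.
Both stated figures reproduce. The sizing therefore fits a two-sample comparison on the plain SD of change.

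**Step 2. Power and interval width as stated.**
Standard error of the difference = 24.13 × √(2/41) = 5.33.
Power at 41 per group is 80.4% by the normal approximation and 79.4% by the noncentral t. The 95% CI half-width is 10.6.

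**Step 3. The same with adjustment for baseline VAS.**
Residual SD = 24.13 × √(1 – r²). Power is from the noncentral t, with 3 further degrees of freedom removed for baseline VAS, age and adenomyosis. No gain is credited to age or adenomyosis, because the article gives nothing from which to size it.

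| r | Residual SD | Power at 41 per group | 95% CI half-width | n per group for 80% power (normal approximation) |
|---|---|---|---|---|
| 0 | 24.13 | 79.4% | 10.6 | 41 |
| 0.3 | 23.02 | 83.0% | 10.1 | 37 |
| 0.5 | 20.90 | 89.4% | 9.2 | 31 |
| 0.6 | 19.30 | 93.5% | 8.5 | 26 |

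At r = 0 the cost of adjusting is negligible.

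**Step 4. Effect of a chance baseline imbalance on the unadjusted estimate.**
A baseline imbalance of one standard error moves the unadjusted difference by r × 5.33, which is 1.6 points at r = 0.3, 2.7 at 0.5 and 3.2 at 0.6. That is about 11%, 18% and 21% of the 15-point margin.

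**Step 5. The two descriptions side by side.**
The Limitations sentence names age and adenomyosis, the same two factors that Data Collection and Study Procedures gives for stratifying the randomisation. It says their effect was balanced allocation. Both features point to stratified randomisation under the wrong name. Read literally, the sentence describes an analysis that the Statistical Analysis section does not contain. It does not mention baseline VAS on either reading.

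**The case against.** **The stated analysis is valid.** Under randomisation the difference in mean change is unbiased, and its interval already allows for chance imbalance on average. Leaving out stratification factors tends to make the interval conservative. A reader might infer an inflated risk of falsely declaring noninferiority, or a wrong sample size. The article supports neither. This objection stands in full: the loss is in precision and in sensitivity to the imbalance that happens to occur.

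**Unadjusted is read from silence.** The article never uses the word, covariates are often left to an analysis plan, and a trial that intends ANCOVA can be sized conservatively on the plain SD. This stands in part. An analysis plan that is not shown may name a model. But the article does state its primary comparison and decision rule, and the Limitations section describes something else, so the two need reconciling in any case.

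**The Limitations sentence is a slip of terminology.** This is the likelier reading. A reader might conclude that a promised protection against bias is absent from the plan. If stratified randomisation was meant, the balancing measure is in the plan. The sentence also lends no support to the power gain, which comes from baseline VAS.

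**The gain could be overstated.** A reader might quote a rise in power to 90–95%. That arithmetic is correct only if baseline and week-48 variances are equal and their correlation is 0.2 to 0.5, which forces r (in absolute value) to 0.50–0.63. With the same correlations and the SD of change held at 24.13, a week-48 SD 1.5 times the baseline SD gives 82–88%, and a ratio of 2 gives 80–84% (normal approximation). A ratio below 1 gives more than 95%. The range in r is the honest summary.

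**Timing.** Changing the primary analysis of an open-label trial after data collection, to one expected to narrow the interval, has a cost in credibility. This stands, and it shapes the fix.

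**Conclusion.** The point holds as a free improvement in precision together with a wording conflict. The stated primary analysis is valid and consistent with the sample size, but it does not use baseline VAS or the stratification factors, all of which are already recorded. With 41 evaluable per group and no true difference, adjustment for baseline VAS would raise t-based power from about 79% to between 83% and 94% for r from 0.3 to 0.6, and bring the 95% CI half-width from 10.6 down to between 10.1 and 8.5. If r is near zero, nothing material is gained or lost. These figures rest on the article's SD of 24.13, on its assumption of equal effects, and on an assumed r. The conflict between Limitations and Statistical Analysis concerns age and adenomyosis only, and most plausibly comes from calling stratified randomisation covariate adjustment.

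**What to change.** 1. **Specify one primary model:** an ANCOVA of week-48 VAS, or of change, on treatment, baseline VAS, age stratum and adenomyosis. Take the adjusted treatment difference and its 95% CI to the stated –15 limit. Keep the unadjusted difference in mean change as a sensitivity analysis.
2. **Fix the timing.** Date and record this before any comparison of the arms, and state that none has been made. If one has already occurred, keep the stated analysis as primary and report the ANCOVA as supportive.
3. **Reconcile the text.** If the Limitations sentence means stratified randomisation, reword it to say so. If an adjusted analysis was intended, state it under Statistical Analysis. In either case, do not credit an analysis model with balancing the allocation.

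The cost is wording in the protocol or analysis plan. No further patients, visits or data are needed, and 88 remains the planned number.

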**Painkiller usage**				
	None	None.	0	
	Slight	Used painkillers for 1 day during menstrual period.	1	
	Moderate	Used painkillers for 2 days during menstrual period.	2	
	Severe	Used painkillers for 3 days during menstrual period.	3	

**Table 2 table2:** Kupperman score.

Symptom	Degree	Evaluation
Hot and sweaty face	3,2,1,0	4
Numbness in the limbs and loss of sensation	3,2,1,0	2
Difficulty falling asleep and waking easily	3,2,1,0	2
Easily agitated and nervous	3,2,1,0	2
Worried and depressed	3,2,1,0	2
Feeling dizzy or nauseous	3,2,1,0	1
Tire easily	3,2,1,0	1
Pain in the shoulders, knees, and knots in the hands and feet	3,2,1,0	1
Headache	3,2,1,0	1
Palpitations	3,2,1,0	1
Feels like ants crawling on the skin	3,2,1,0	1

To determine the score, multiply the “Degree of Symptomatology” (Degree) number by the “Rating Scale” number (Evaluation).

Scoring is classified as follows: mild disease: 16-20, moderate: 21-34, and severe: 35 and above. Degree is defined as strong: 3, moderate: 2, weak: 1, and none: 0.

Patients will be allowed to use analgesics for the management of dysmenorrhea-related pain as needed. Bone density assessments will be conducted twice, at the beginning and end of the study period, using dual-energy x-ray absorptiometry.

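### The Statistical Analysis section does not name the secondary endpoints as defined: it compares a mean value for bone density, Kupperman score and estradiol where the endpoints are changes from baseline, which would matter for bone density if followed literally

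*Protocol article*

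**What the plan says.** Study Endpoints lists the further safety endpoints as "the amount of change in the Kupperman score, the rate of change in bone density, and the amount of change in blood estradiol concentration", measured from baseline to 48 weeks. Among the secondary efficacy endpoints, the dysmenorrhea score is also defined as an amount of change over that period, and the cyst endpoint is "the rate of reduction in the size of ovarian endometriotic cysts from the baseline to 48 weeks after administration".

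Statistical Analysis words the comparisons differently. For safety, the groups are compared to "estimate the difference and its 95% CI for the mean value of bone density, Kupperman score, and estrogen concentration"; the sentence mentions neither change nor a time point. For secondary efficacy, the difference and its interval are estimated "for the mean value of dysmenorrhea score and change in endometriotic cyst size from baseline to 48 weeks". The primary analysis, by contrast, names its variable fully, as "comparing the change in VAS from baseline to 48 weeks between the dienogest 1 mg/day group and 2 mg/day group".

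On data, the section on Data Collection and Study Procedures (text after Table 2) states: "Bone density assessments will be conducted twice, at the beginning and end of the study period". Both values needed for a change in bone density are therefore planned.

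**The concern.** An endpoint and its analysis should be the same variable. Here the endpoint section gives one set and the analysis section states another for all three continuous safety endpoints. This is not a detail left to a later document, because the analysis section does name a quantity and it differs from the endpoint.

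Bone density has the most at stake. The Discussion expects less bone loss on 1 mg/day. A one-year loss is small beside the differences between women at any one time, so a comparison of raw week-48 means could be too imprecise to say anything about that expectation.

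For cysts, the word change does not say whether it is relative or absolute. Two women with the same proportional shrinkage have different absolute changes if their cysts differed in size at baseline.

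Timing adds to the concern. The Results section reports that data collection is complete and the data are being fixed for analysis. In an open-label trial, two admissible readings leave a choice of variable open at that stage.

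**Working it through.** **1. The plan's own figure.** The Sample Size section uses margin 15, SD 24.13, one-sided 2.5% and 80% power on VAS:

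n per group = 2 × (1.96 + 0.84)² × 24.13² / 15² = 40.6, so 41; and 41 / 0.95 = 43.2, so 44.

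Both stated figures reproduce. The plan states no precision or power for bone density, Kupperman score or estradiol, so there is no further figure to check.

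**2. Endpoint against analysed quantity.**

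| Variable | Study Endpoints | Statistical Analysis |
|---|---|---|
| Bone density | rate of change | mean value |
| Kupperman score | amount of change | mean value |
| Estradiol | amount of change | mean value |
| Dysmenorrhea score | amount of change | mean value beside a change; the scope of the word change is unclear |
| Cyst size | rate of reduction | change, relative or absolute not stated |

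**3. Bone density, percent change.** The Discussion quotes a cited study of 2 mg/day with a 52-week change of mean –1.7%, SD 2.2%. Applying that SD to both arms, with 41 women per arm:

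SE = 2.2 × √(2/41) = 0.486; half-width = 1.96 × 0.486 = 0.95 points.

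**4. Bone density, raw 48-week means.** The documents give no between-woman SD, so it is assumed at 5%, 10% and 15% of the mean. Half-width = 1.96 × SD × √(2/41):

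| Assumed SD | Half-width (points) | Ratio to percent change (SD / 2.2) | Information lost, 1 – (2.2 / SD)² |
|---|---|---|---|
| 5% | 2.2 | 2.3 | 81% |
| 10% | 4.3 | 4.5 | 95% |
| 15% | 6.5 | 6.8 | 98% |

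More than half the information is lost once the SD exceeds 2.2 × √2 = 3.1% of the mean. Using the t quantile instead of 1.96 widens every interval by the same factor (0.95 becomes 0.97) and leaves the ratios unchanged.

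**5. Kupperman score and estradiol.** With equal variances at the two visits and baseline-to-week-48 correlation r, the variance of the change divided by that of the final value is 2(1 – r): 1.4 at r = 0.3, 1.0 at r = 0.5 and 0.4 at r = 0.8. Change is more precise only if r exceeds 0.5, and the documents give no r. Baseline-adjusted ANCOVA has relative variance 1 – r², which is never above 1 and never above 2(1 – r).

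**The case against.** The strongest reply is that the phrase is shorthand. The article is condensed, the endpoints have just been defined as changes, bone density is measured at both ends of the study, and the preceding efficacy sentence joins the same mean-value wording to a change from baseline. This reply stands as far as intent goes. A reader might infer that the plan throws the baseline measurement away, but no sentence says so; that follows only from the literal wording. The reply does not remove the mismatch. The same section writes change explicitly for VAS and cyst size and omits it in the safety sentence, and even the shorthand reading leaves percent change in bone density unnamed.

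Other stronger readings also lack support:

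- A reader might infer that cysts are analysed as absolute change. The text says only change, which is compatible with a relative measure.
- A reader might infer that a well-powered bone comparison is being lost. Power with percent change reaches 94% (41 per arm, SD 2.2%) only for a 1.7-point difference. That equals the whole one-year loss quoted for 2 mg/day and so assumes no loss on 1 mg/day, whereas the Discussion expects only less loss. For half that difference, 0.85 points, power is about 42% even with percent change.
- A reader might infer that a null result would be taken as equal bone safety. The plan gives a difference with an interval here and names no test, and a wide interval would itself show the imprecision.

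Finally, these are secondary safety analyses. The safety endpoint the plan marks as important is the incidence of low-estrogen symptoms, which this point does not touch.

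**Conclusion.** The point holds as a mismatch between the endpoint and analysis sections: definite for the wording of the three continuous safety endpoints, and a lesser lack of alignment for dysmenorrhea score and cyst size. Its practical weight lies with bone density and is conditional on the literal reading. There the interval would be about 2.3 to 6.8 times wider than for percent change, over assumed between-woman SDs of 5% to 15%. That range is an assumption, and the 2.2% SD comes from a cited study at the higher dose and is applied to both arms. No loss of precision can be shown for Kupperman score or estradiol. The primary noninferiority conclusion and the sample size of 88 are unaffected.

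**What to change.** Before the analysis is run, correct the Statistical Analysis section so that it compares the variables in Study Endpoints, all from baseline to 48 weeks: percent change in bone density, change in Kupperman score, change in estradiol, change in dysmenorrhea score and percent reduction in cyst size. Estimate each group difference and its 95% CI by ANCOVA, adjusting for the baseline value of that variable and the randomisation strata (age and adenomyosis). If any comparison by group has already been seen, the report should say that the wording was settled afterwards.

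Log ratios to baseline are not needed. For estradiol they would depart from the defined amount of change, and for a cyst that resolves completely the log ratio is undefined.

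The cost is a wording correction and modest programming. Baseline and week-48 values are already in the plan, so no additional patients, visits or measurements are needed.
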